### Interim analyses

As virtual reality technology is not known to be associated with severe adverse events and because the present intervention is designed for one session, 15 min length, there has no planned interim analyses or stopping rules.

### Oversight and monitoring

From the study group, RG and HS were responsible for the supervision of data acquisition. In this vein, they had weekly meetings with the research assistant responsible for data collection to monitor the entire process. A Data Monitoring Committee was not employed as the study implementation was designed in one site and the intervention has a low risk for adverse effects. Any change from the protocol will be reported to the ethical committee of the Babeș-Bolyai University and will be updated in the ClinicalTrials.gov (NCT03776344).

## Discussion

Treating pain after surgical interventions is an overly complex and challenging process (61,62), and the integration of non-pharmacological approaches has been one of the priorities of healthcare reform in the last years [5]. Additional interventions along the standard pharmacological treatments are strongly recommended by the guidelines for postoperative pain management [5]. Limited medical personnel resources and short periods of hospitalization are widely known problems of the postoperative management, highlighting the need for additional interventions that are requiring very little set-up time to co-occur with the standard pharmacological treatment. Addressing these problems, VR interventions can be used as a non-pharmacological tool for reducing pain after surgery. The present protocol offers a detailed description of a randomized and controlled clinical trial to determine the effectiveness of VR environments in reducing pain intensity in surgical patients.

Should the hypotheses suggested in this study be proven, this would add empirical evidence about the benefits and feasibility of VR for the pain treatment in surgical patients. Our expectation is to obtain greater pain relief compared with studies employing non-technological interventions. Moreover, we expect that the results of the present study to be in line with the ones conducted by Mosso-Vazquez and colleagues [32] as well with studies that use VR for non-surgical patients [29, 30]. In addition, we expect to find minimal side effects in those patients exposed to VR and the level of willingness to use VR sessions in the future treatment of pain to be high.

However, the present protocol is exposed to several threats. First, by recruiting participants from o single hospital is possible to affect the external validity of the study. Will be unknown if the characteristics of our participants will be representative for a broader population of surgical pain suffers. Moreover, our results cannot be extrapolated to other VR environments, being strictly linked to Nature TreksVR®. Second, the present protocol uses self-reported measures to asses pain intensity, level of relaxation, mood, pain catastrophizing and an open-label design, thus is possible that some of the reports be affected by the knowledge of the group assignment. Nonetheless, the trial assessors and researchers conducting data analysis will be blinded in order to improve the internal validity of the study and maintain a low detection bias (63). Not lastly, our results will be subtracted in the absence of other non-pharmacological treatment, thus, in the case of hypothesis confirmation we can conclude that the Nature TreksVR® produce significant reductions in pain intensity but we cannot know the effects when other non-pharmacological interventions are applied or when VR-based interventions are integrated in more comprehensive treatments of pain intensity.

Concluding, although several threats exist, this study is to our knowledge, the first to test the efficacy of a modern, market-ready VR application for the treatment of pain after surgery, and his results will assist in the development of a new method for the delivery of evidence-based treatments.

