### Randomization and blinding

Randomization was conducted within the type of surgery using a random number generator, with an equal number of participants in the control and experimental group. An independent researcher had conducted the randomization sequence and the allocation sequence was stored on a secured computer until the participants were assigned to one of the interventions. The medical personnel and trial assessors were blind to the group allocation, but the study participants and research assistant were aware of the allocations. Precaution strategies to prevent the blind from breaking up included a limited number of persons interacting with the patients (i.e. only the research assistant) and a reminder to the patients not to talk about research allocations and study procedure. In addition, the treatment room was a different room of the patient hospital room. In the treatment room patients from the experimental group was exposed to the VR content and psychological respectively physiological measured. For the patients from the control group, only psychological and physiological measures were taken without exposing them to the VR content. After this, each participant was conducted to their hospital room. In the case that a participant explicitly requests to end the study procedure for any reasons, the procedure was stopped and counted as a dropout. Those patients who ask to end the procedure earlier were asked to respond at a short interview to quantify the reasons.

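### Blinded assessors and analysts cannot keep detection bias low for the primary outcome, because NRS pain is rated by patients who know their arm

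*Protocol article*

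**What the plan says.** The section on randomization and blinding in the protocol article states: "The medical personnel and trial assessors were blind to the group allocation, but the study participants and research assistant were aware of the allocations". Among its precautions against unblinding it lists "a limited number of persons interacting with the patients (i.e. only the research assistant"), together with a reminder to patients not to discuss their allocation.

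The section on oversight and monitoring says that two study supervisors held "weekly meetings with the research assistant responsible for data collection to monitor the entire process".

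The outcomes section makes pain intensity before and after exposure the primary outcome. The measures section specifies a 0-10 NRS that participants are asked to complete.

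The Discussion lists self-report and the open-label design as a threat, and accepts that knowledge of the assigned group may affect some reports. It then offsets the threat: "the trial assessors and researchers conducting data analysis will be blinded in order to improve the internal validity of the study", and to "maintain a low detection bias".

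**The concern.** The Discussion names the right limitation and then reassures the reader with a safeguard that does not apply to the outcome at issue. Detection bias arises when knowledge of allocation influences how an outcome is assessed. For a self-rated score the patient makes the assessment, so masking anyone else leaves the main route open.

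What is at stake is interpretation. The Discussion says that, if the hypothesis is confirmed, the investigators can conclude that the VR application significantly reduces pain intensity. Controls sat in the same kind of measurement session without VR. A modest NRS difference could therefore reflect expectation or reporting as well as analgesia. A results paper that inherits the low-detection-bias statement would claim a protection that its primary outcome does not have.

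**Working it through.** The document states no figure on this point that could be reproduced, so the check sets its sections side by side.

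1. **Who rates the primary outcome?** The patient, on the NRS (outcomes and measures sections). Relaxation, time spent thinking about pain and the simulator sickness items are also patient ratings.
2. **Is the rater masked?** No. The randomization and blinding section says that participants knew their allocation.
3. **Is the collector masked?** Not on the text. The same section limits patient contact to the research assistant and says that the assistant knew the allocation. The oversight section makes the research assistant responsible for data collection.
4. **Could someone else be the blinded assessor?** The data collection section says that a trained researcher collected all psychological and physiological measures and met the supervisors weekly. The oversight section describes weekly meetings between the same two supervisors and the research assistant, so this is most likely one person. If it were a second person, that would conflict with contact being limited to the research assistant. On either reading the patient is still unmasked.
5. **Does the online platform change this?** The data collection section says that everything except skin conductance went through an online platform, without saying who entered the scores. Entry by the patient would limit the assistant's influence. It would not remove the patient's own knowledge of the arm.
6. **What can analyst blinding do?** It protects choices made during data handling and modelling. It cannot correct scores that already carry a reporting shift.

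**Illustration only.** The document gives no size for such a shift, so a range is assumed. Inputs: 30 per arm (the recruitment target in the sample size section), no true effect, a two-sided 5% two-sample t-test, and a shift of b standard deviations due purely to reporting. Degrees of freedom are 2 × 30 − 2 = 58. The noncentrality is b × √(30/2) = 3.873 × b. The rejection rate is the probability that a noncentral t variable lies outside the two-sided 5% limits.

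| Assumed shift b (SD) | Noncentrality | Rejection rate, 30 per arm | Rejection rate, 25 per arm |
|---|---|---|---|
| 0 | 0 | 5.0% | 5.0% |
| 0.1 | 0.39 | 6.7% | 6.4% |
| 0.2 | 0.77 | 11.9% | 10.7% |
| 0.3 | 1.16 | 20.8% | 18.0% |
| 0.49 | 1.90 | 46.3% | 39.7% |

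The last row uses a shift as large as the effect assumed in the sample size section. The planned analysis is a random coefficient model with a time-by-group term, so the t-test is a simplification. The rates describe open-label self-report in general. They show what the blinding statement fails to protect against, and are not an estimate of bias in this trial.

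**The case against.** The strongest reply is that the document is already candid. It says that patients and the research assistant knew the allocation, calls the design open-label, and concedes that reports may be affected. This stands: the limitation is not hidden. What remains is the sentence that follows the concession and offsets it.

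A second reply is that the term trial assessors is undefined and could mean people who process skin conductance or extract charts. This also stands. The text does not show that no blinded assessor exists anywhere, only that none is described for the primary outcome.

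A third reply is that the stated question is VR added to standard care versus standard care alone, so expectation may count as part of the add-on effect. That is a legitimate estimand, but it does not cover pure reporting bias and does not make detection bias low.

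A reader might go further and infer that analyst blinding fails, because the presence and willingness items would reveal the arm and the raw skin conductance signal is inspected by eye. The document does not support this. Nothing in it contradicts blinded analysis. That only VR patients have presence data is plausible but inferred: controls are said to follow the same protocol for psychological measures, and the schedule figure is not shown. Visual inspection says nothing about whether the inspector knows the arm. How files are separated is commonly left to an analysis plan.

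**Conclusion.** The point holds in a limited form. The statements that trial assessors were blind and that detection bias stays low do not hold for NRS pain or the other patient-reported outcomes, whoever entered the scores. The conclusion rests on two things that the document states: the outcome is self-rated, and patients know their arm. The research assistant's role strengthens it, and taking the trained researcher to be the same person is likely but not essential.

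The size of any bias cannot be derived from the document. The outcome, sample size and model need not change. The consequence is a limit on what a pain difference can be said to show. Skin conductance is listed with the primary measures and could be scored masked, but it does not rescue the claim: the analysis section names pain intensity as the primary outcome and plans for skin conductance only a difference score and a correlation with pain change.

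**What to change.** 1. Withdraw the low-detection-bias statement for NRS pain and the other patient-reported outcomes. Possible wording: *Pain and the other questionnaire outcomes are unblinded patient reports, so detection bias cannot be excluded.* Align the randomization and blinding section with this, and state who the trial assessors are and what they assess.
2. Limit the blinding claim to steps that can be masked: inspection and scoring of skin conductance, coding of opioid use from charts, and the primary model run on coded arm labels. As a low-cost precaution, hold back any VR-specific presence and willingness items until that model is final. This is not a correction of a shown error.
3. Qualify the planned conclusion, so that a pain difference is read as the effect of adding VR to standard care under open-label self-report, which may include expectation or reporting effects.

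**Cost:** text changes and separate data files. Recruitment ended in September 2019, so collection cannot change. The trial status section says that opioid data had not been extracted and analysis had not been performed, so the masked steps remained feasible on that account.

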### Data storage

During data collection, all the data will be safely stored at the Municipal Hospital. After the implementation phase is completed, all the data will be transferred in a secured PC at the International Institute of Psychotherapy, accessible only by the principal investigator (RG) and the corresponding author (AD).

### Dissemination

Following the recommendations of the Consolidated Standards of Reporting Trials (CONSORT) [57] statement for reporting RCTs, results will be submitted to a peer-reviewed journal and presented as oral or poster presentation at international scientific conferences. Additionally, we will make available all the results to patients if required. After the results are published in a peer-review journal, all the materials used will be made public at request. The datasets corresponding to the current study are available from the corresponding author on reasonable request.

## Trial status

The trial started patient recruitment in October 2018 and completed in September 2019. At the date when the first draft of the present protocol was submitted (March 2019) the status of data collection was “on going.” Currently, the data for opioid consumption were not extracted from the patient medical records, and data analysis was not performed. A trial paper with the results should be submitted for publication around the beginning of 2021. The present version of the protocol is 1.5 (March 2021).

## Data Availability

Not applicable

## Abbreviations

RCT: Randomized controlled trial
VR: Virtual reality
IASP: International Association for the Study of Pain
CPSP: Chronic post-surgery pain
CBT: Cognitive behavioral therapy
HMD: Head-mounted display
SPIRIT: Standard Protocol Items: Recommendations for Interventional Trials
SC: Skin conductance
NRS: Numerical Rating Scale
VAS: Visual analog scales
SSQ: Simulator Sickness Questionnaire
SEQ: Suitability Evaluation Questionnaire
PCS: Pain Catastrophizing Scale
HADS: Hospital Anxiety and Depression Scale
6CIT: Six-item Cognitive Impairment Test
